### Data analysis

Educators’ and parents’ responses to questionnaires will provide detailed data to assist us to determine whether *Partnering with Parents* is effective in increasing educators’ confidence and skills in partnering with parents. We propose a number of ways to examine the process and outcome data.

First, we will use confirmatory factor analysis using baseline data to confirm the internal validity of scales, developed using questionnaire items, to represent the outcome measures of interest. We will check commonly used goodness of fit requirements (e.g. RMSEA<.08, CFI > 0.90, TLI > 0.90) as recommended by Bryne [23]. Data for items missing completely at random will be imputed using the EM algorithm for each assessment period, with the reliability of the resulting summated scales computed using Cronbach alpha, with values of above 0.70 deemed to be acceptable.

Second, we will perform descriptive analyses of questionnaire responses to explore the nature of the data. For example, we will examine distribution properties of the scales to inform decisions about the need for any transformations before statistical analysis of between-group differences. We will also examine how participants in the trial compare with other samples, for instance, where normative data are available (such as the Parenting Today in Victoria survey results and the Me as a Parent scale data), we will compare trial participants’ responses with population norms for parents of children of similar ages.

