### Blinding

Cluster RCTs are typically not blinded as intervention is usually delivered at the cluster level. In other words, throughout the trial, educator participants will know whether they are in the intervention or control group. Parent participants may or may not know, depending on whether the services choose to inform them. We are aware of this design limitation, but it is unavoidable. Researchers who are involved in training educators will know which services are in the intervention or control group. However, the researchers who analyse outcome data will be blind to intervention allocation. To facilitate this blinding, a researcher who is independent to the data analysis will create a code to identify whether a service is in the intervention or a control group. This code will not be known to the researchers conducting the analysis.

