### Baseline analysis (time 1)

As a check for appropriate balance between the control and intervention groups and to provide an overview of the study population [24], both at service and individual levels, data for the control and intervention groups will be compared at baseline. We will present the mean, standard deviation and range for continuous, approximately symmetric variables; medians, interquartile range and range for continuous, skewed variables of clusters. We will describe categorical data with percentages across sub-groups.

All statistical tests and confidence intervals will be two-sided. Between-group comparisons will be presented with 95% confidence intervals and the statistical significance level set will be at the 5% level. In addition, we will account for the clustered nature of the data for all comparative analyses to ensure correct confidence intervals and type I error rates are calculated. In addition, the intra-cluster correlation coefficient for each outcome, based on the adjusted analyses with 95% confidence interval, will be reported.

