### Analysis of primary and secondary outcome measures

An intention-to-treat multi-level analysis will be conducted for each of the outcome measures with level 1 data reflecting each assessment period, level 2 data reflecting individual participants and level 3 data reflecting the various services. Changes in the outcome measures will be compared for the intervention and control groups assuming appropriate distributions for the outcome measures. Random intercepts will be assumed, while allowing for the clustered nature of the data, and adjusting for appropriate covariates as fixed effects. The model will include an indicator variable for the study groups (0 = control, 1 = intervention) as a fixed effect at level 3 and an integer time variable (1 = baseline, 2 = time2 and 3 = time3) as a random effect at level 1.

We will report the estimated intervention effect as mean outcome difference for continuous outcomes and odds ratio for binary outcomes between intervention and control groups with 95% confidence intervals and *p*-values [25]. The effect of individual moderators will be incorporated using interaction terms between time, allocated group and the individual moderators [26].

Finally, a completer analysis will be conducted with a repeated measures MANOVA analysis using inverse probability weights to adjust for any attrition bias [27]. This analysis will also account for the correlation between measures from the same participant, while allowing for the clustered trial design.

Furthermore, we will examine responses of the control group before and after receiving the intervention.

As an indication of family-centredness, we will look at items that both educators and parents completed, to compare their perceptions (e.g. whether they both agree the service is a welcoming environment for parents).

All qualitative data (open text questions) will be summarised and examined for themes. Thematic analysis is a multi-stage process involving familiarisation with the data, coding (identifying important features relevant to the research questions), searching for and reviewing themes, and defining and naming them [28].

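### Cronbach alpha is computed after EM filling of missing items, which on the usual reading biases it upward against the plan's own 0.70 line and shrinks the scale scores' variance

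*Protocol article*

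**What the plan says.** The Data analysis section sets out three steps for the scales. For construct validity, "we will use confirmatory factor analysis using baseline data to confirm the internal validity of scales". For blank items, "Data for items missing completely at random will be imputed using the EM algorithm for each assessment period". Reliability follows in the same sentence, "with the reliability of the resulting summated scales computed using Cronbach alpha, with values of above 0.70 deemed to be acceptable". So alpha is a property of the scales after filling, and 0.70 is the line they must pass.

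The section on analysis of primary and secondary outcomes then uses the scale scores in a three-level model: "An intention-to-treat multi-level analysis will be conducted for each of the outcome measures with level 1 data reflecting each assessment period", with "an integer time variable (1 = baseline, 2 = time2 and 3 = time3) as a random effect at level 1". Whole missing questionnaires are treated separately: "a completer analysis will be conducted with a repeated measures MANOVA analysis using inverse probability weights to adjust for any attrition bias".

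The article does not say whether the EM fill is single or carries a random residual, or whether arm, service or other waves enter it.

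**The concern.** As usually run, EM imputation replaces a blank item by its expected value given the person's other items. A value filled that way has no residual scatter and lies exactly on the regression on the other items. Alpha measures how well items hang together, so filled items make the scale look more coherent than the respondents were. The bias always runs toward acceptance.

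Many items were devised by the project team or adapted from other surveys (Educator questionnaire; Parent questionnaire), so the reliability check carries real weight. The same fill also makes the outcome scores less variable than the true scores. Depending on how it is run, it may affect the arm comparison at follow-up. Filling each wave alone ignores the same person's answers at other waves, although the main model links them.

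**Working it through.** **Inputs.** From the article: EM fill by wave, alpha afterwards, line at 0.70 (Data analysis); 302 parents and effect size 0.5 (Power analysis); 118 educators (Participants). Assumed, because the article gives none: 5%, 10% or 20% of items missing completely at random; five equally correlated normal items; complete-data alpha 0.70; a fill at the conditional mean. The plan has no figure of its own to reproduce on this point.

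**Step 1, by hand.** With k items of variance 1 and common correlation r, alpha = kr / (1 + (k − 1)r). Setting alpha = 0.70 and k = 5 gives r = 0.70 / (5 − 4 × 0.70) = 0.318.

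- Variance of one item explained by the other four: 4r² / (1 + 3r) = 0.405 / 1.955 = 0.207. A filled item therefore loses 0.793 of its variance.
- Complete data: the item variances sum to 5 and the total score variance is 5 + 20r = 11.364.
- With a fraction m missing, and ignoring people with several blanks, both fall by 5m × 0.793 and the covariances are unchanged. Alpha becomes 1.25 × (1 − item sum / total).
- m = 5%: 1.25 × (1 − 4.802 / 11.165) = 0.712; variance ratio 11.165 / 11.364 = 98.3%.
- m = 10%: 1.25 × (1 − 4.604 / 10.967) = 0.725; ratio 96.5%.
- m = 20%: 1.25 × (1 − 4.207 / 10.571) = 0.753; ratio 93.0%.

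**Step 2, by simulation** (302 people, two equal arms, no arm effect, arm omitted; 700 replicates at 5% and 20%, 300 at 10%), which allows several blanks per person:

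| Missing | Alpha, complete | Alpha, filled | Alpha, EM covariance | Score variance ratio |
|---|---|---|---|---|
| 5% | 0.699 | 0.711 | 0.699 | 98.0% |
| 10% | 0.699 | 0.723 | 0.699 | 96.3% |
| 20% | 0.699 | 0.745 | 0.697 | 91.6% |

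The hand figures agree closely at 5% and 10%. At 20%, multiple blanks per person matter and the simulation is the better guide. The EM covariance matrix shows almost no bias. With 118 people, six items and inter-item correlation 0.3, alpha rose from 0.73 to 0.74, from 0.725 to 0.746 and from 0.73 to 0.77 at the three rates.

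**Step 3, the 0.70 line.** For a weaker scale (60 replicates per setting, arm effect present), alpha went from 0.671 to 0.684 at 5%, from 0.667 to 0.693 at 10% and from 0.663 to 0.714 at 20%. A scale near 0.66 crosses only at about 20% missing. A scale at about 0.69 needs only the 0.01 rise seen at 5%.

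**Step 4, the arm comparison at follow-up** (true difference 0.5, complete-data estimate 0.497; 700 replicates):

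| Imputation model | Missing | Estimate | Standard error / empirical SD |
|---|---|---|---|
| Arm omitted | 5% | 0.489 | 1.01 |
| Arm omitted | 20% | 0.457 | 1.02 |
| Arm included | 5% | 0.497 | 0.99 |
| Arm included | 20% | 0.496 | 0.945 |

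The complete-data ratio is about 1.01. With arm omitted, the shrinkage is 1 − 0.489 / 0.497 = 1.6% and 1 − 0.457 / 0.497 = 8.0%. With no true effect and 20% missing, rejection was 6.1% on complete data, 6.6% with arm omitted and 7.9% with arm included. The Monte Carlo error is about √(0.06 × 0.94 / 700) = 0.9 percentage points, so these rates are only indicative. Clustering by service was not simulated.

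**The case against.** The strongest reply is that the article is silent on what drives part of the problem. It does not say the fill is single or without residual, nor that arm and service are left out. Such detail commonly sits in a fuller analysis plan. This stands for the arm comparison, which is why that part is stated as two alternatives. It does not dispose of the alpha point: the article itself fixes both the method and the order, fill first and reliability second.

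The effects are also small unless item non-response is high. This stands too. Nothing in the article suggests 20% blanks in a questionnaire of 10–15 minutes, and the factor-analysis fit criteria are a second check on the scales.

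A reader might infer three stronger things that the documents do not support:

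- *Arms pulled together and standard errors too small at once.* Each belongs to a different imputation model, and the two did not occur together in the check.
- *A distorted comparison at every wave.* Time 1 precedes randomisation, so there is no arm effect to attenuate at baseline.
- *That imputing only items missing completely at random is the wrong way round.* Filling such items legitimately preserves sample size, since one blank otherwise loses a summed score. The article does not say that other missing items will be discarded.

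**Conclusion.** The point holds as a small one. The stated order of steps biases the plan's own reliability check in the direction of acceptance and lowers score variance, by the amounts in the table under Step 2. This rests on the usual conditional-mean reading of EM imputation and on assumed missing rates, item numbers and true alpha. At 5% or fewer missing items only a scale already within about 0.01 of the line is affected.

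The consequence for the treatment comparison is conditional and applies only after Time 1. It is either modest attenuation with a sound standard error, or no attenuation with a standard error slightly too small. The documents do not settle which, so neither can be claimed as a defect of the plan as written.

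**What to change.** Two changes to the analysis plan:

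1. Compute alpha from the observed items or from the EM covariance matrix, which the algorithm produces anyway, and not from the filled data.
2. For the outcome scores, choose one of two routes. Score each scale as the mean of answered items when at least half are answered; a check of this scoring showed no attenuation, though it assumes that items within a scale have similar means. Or use item-level multiple imputation under missing at random, including coded arm, service and the person's other waves.

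The coded arm is compatible with the Blinding section, under which "the researchers who analyse outcome data will be blind to intervention allocation", because an independent researcher holds the code. Whole missing questionnaires can stay with the multilevel model and the weighted completer analysis, as already planned.

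The cost is a sentence or two. Mean-of-answered scoring adds no work; multiple imputation adds a little analysis time. According to Trial status and Data Availability, Time 2 data were still being collated and no datasets had been analysed when the article was written, so at that stage the change could be made before any outcome result was known.

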### Baseline analysis (time 1)

As a check for appropriate balance between the control and intervention groups and to provide an overview of the study population [24], both at service and individual levels, data for the control and intervention groups will be compared at baseline. We will present the mean, standard deviation and range for continuous, approximately symmetric variables; medians, interquartile range and range for continuous, skewed variables of clusters. We will describe categorical data with percentages across sub-groups.

All statistical tests and confidence intervals will be two-sided. Between-group comparisons will be presented with 95% confidence intervals and the statistical significance level set will be at the 5% level. In addition, we will account for the clustered nature of the data for all comparative analyses to ensure correct confidence intervals and type I error rates are calculated. In addition, the intra-cluster correlation coefficient for each outcome, based on the adjusted analyses with 95% confidence interval, will be reported.

### Attrition analysis

We will calculate the proportion of missing data at the individual and cluster level. Observed and expected attrition rates will be compared for each assessment across clusters. We will not consider any data that were not available because of withdrawal of consent for data use by participants. We will use binary logistic regression to model attrition at Times 2 and 3 in terms of baseline measures and demographic characteristics. Predicted attrition probabilities for both these time points will be computed for use in completer analyses.

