### Data collection timepoints

The following measures will be collected online via a secure data system at three time points: Time 1 = 0 weeks (before randomisation to trial conditions), Time 2 = at the end of week 10 (immediately after the intervention group has completed the intervention), and Time 3 = 3 months after the intervention group has completed the intervention and immediately after the control group has completed the intervention. Each questionnaire takes about 10–15 min to complete. To thank participants for their time, after completing the third questionnaire they will be able to download a tailored package of resources about early childhood and development produced by the PRC.

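### The attrition model behind the completer-analysis weights omits allocated arm, so the weights cannot correct arm-dependent attrition; the main intention-to-treat analysis is not affected.

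*Protocol article*

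**What the plan says.** The protocol article's Attrition analysis section names two classes of predictor: "We will use binary logistic regression to model attrition at Times 2 and 3 in terms of baseline measures and demographic characteristics". It then gives the purpose: "Predicted attrition probabilities for both these time points will be computed for use in completer analyses". Under Analysis of primary and secondary outcome measures, the last quantitative outcome analysis is described thus: "a completer analysis will be conducted with a repeated measures MANOVA analysis using inverse probability weights to adjust for any attrition bias".

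Three other statements bear on the point.

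- Allocation cannot count as a baseline measure, since Data collection timepoints defines "Time 1 = 0 weeks (before randomisation to trial conditions"). The educator and parent demographics listed in the article do not include it either.
- The outcome model, by contrast, explicitly contains a study-group indicator.
- The lead analysis is a different one: "An intention-to-treat multi-level analysis will be conducted for each of the outcome measures". The weighted MANOVA is additional to it.

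**The concern.** The weights are meant to deal with attrition bias without qualification ("using inverse probability weights to adjust for any attrition bias"). In a comparison of two arms, the attrition that matters most is the kind that differs between them.

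The design makes that plausible. On blinding, the article says that "throughout the trial, educator participants will know whether they are in the intervention or control group", and parents may know too. Questionnaires are voluntary. At Time 2 one group has just finished a ten-week programme while the other is still waiting. The Discussion accepts that staff may have underestimated the time needed.

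If retention differs by arm, a model fitted to baseline and demographics alone gives two completers with the same profile the same weight, whichever arm they are in. The weighted sample then resembles the pooled baseline sample, but the arms are made no more alike. The weighted and unweighted completer results would tend to agree whether or not bias is present, and a reader could take that agreement as evidence of robustness.

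**Working it through.** **Plan's own figures.** The plan gives no figure for attrition bias, so there is none to reproduce. The only figure used from it is the effect size d = 0.5 (Power analysis), as a yardstick. The required effective sample size of 102 in the same section plays no part here. It reproduces with a one-sided t-test but not with a two-sided one (126 by normal approximation, 128 by t), which is a separate matter.

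**Algebra.** Let X be the standardised baseline score with density f(x), let πₐ(x) be the probability of completing in arm a, and let w(x) be a weight that depends on X only. The weighted density of X among completers in arm a is proportional to f(x)·πₐ(x)·w(x). Between arms, the ratio of these densities is proportional to π₁(x)/π₀(x), because w(x) cancels. That ratio creates the imbalance, and arm-free weights leave it as it was.

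**From imbalance to bias.** Let Δ be the weighted mean of X in intervention completers minus that in control completers. With no true effect, pre-post correlation ρ, equal variances, and completion depending only on X and arm:

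- bias in the follow-up score difference = ρ·Δ
- bias in the difference in change from Time 1 = (ρ − 1)·Δ

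The second is the relevant one. Trial outcomes states the hypothesis as greater change from Time 1 to Time 2, and the group-by-time term of a repeated measures MANOVA compares change.

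**Assumed inputs (not in the documents).** ρ = 0.6 and logistic completion, with no clustering in this large-sample calculation.

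- (a) Retention is 80% in control and 60% in intervention; the log-odds of retention rise 0.5 per baseline SD in both arms.
- (b) Retention is 70% in both arms; the log-odds rise 0.7 per SD in the intervention arm only.

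Numerical integration gives Δ, and change bias = −0.4·Δ:

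| Weights | (a) Δ | (a) change bias | (b) Δ | (b) change bias |
|---|---|---|---|---|
| None | 0.093 | −0.037 | 0.192 | −0.077 |
| Baseline only, as written | 0.100 | −0.040 | 0.204 | −0.082 |
| Baseline + arm | 0.000 | 0.000 | 0.204 | −0.082 |
| Baseline + arm + arm-by-baseline | 0.000 | 0.000 | 0.000 | 0.000 |

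Monte Carlo runs of the same settings gave 0.034 to 0.037 SD in (a) and 0.077 to 0.087 SD in (b), in absolute value, over unweighted and arm-free weighting. As a share of d = 0.5: 0.034/0.5 = 7% up to 0.087/0.5 = 17%.

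**Other settings, ρ = 0.5.** Here follow-up and change bias have the same absolute size.

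| Attrition in the two arms | None | Baseline only | + arm | + arm-by-baseline |
|---|---|---|---|---|
| 25% v 34%, same selection | 0.026 | 0.029 | 0.000 | 0.000 |
| 18% v 50%, same selection | 0.086 | 0.094 | 0.000 | 0.000 |
| 18% v 46%, selection in one arm | 0.160 | 0.174 | 0.115 | 0.000 |
| 30% v 30%, opposite selection | 0.169 | 0.169 | 0.169 | 0.000 |
| 30% v 30%, no arm effect | 0.000 | 0.000 | 0.000 | 0.000 |

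In none of these settings do arm-free weights reduce the bias. An arm main effect alone is not enough when selection on baseline differs by arm. The bias is also zero if arm only multiplies the completion probability by a constant at every baseline value.

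**The case against.** **The main result is protected.** A reader might infer that the trial's principal estimate is biased. The documents do not support that. The lead multilevel model uses all assessment periods, has arm as a fixed effect and does not use these weights. Fitted by likelihood with a group-by-time term (a reading of the plan's comparison of changes), it is valid when dropout depends on observed baseline and arm. A check at n = 20,000 with no true effect gave estimates of −0.005 (SE 0.015) in (a) and −0.008 (SE 0.015) in (b). This objection stands and limits the point to the supplementary analysis.

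**Attrition is also examined elsewhere.** It would be wrong to call the weighted MANOVA the only check. The Attrition analysis section also reports missing data at individual and cluster level and compares observed with expected attrition across clusters, which could reveal a difference between arms. This stands too, but describing a difference does not correct it.

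**The size depends on the contrast.** The follow-up score bias under arm-free weights, 0.6 × 0.100 = 0.06 and 0.6 × 0.204 = 0.12 SD, looks larger. The planned hypothesis concerns change, so the smaller figures apply, with the opposite sign.

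**Differential attrition is assumed.** No arm-specific retention is given. The workload argument fits educators better than parents, who may not know their arm. This stands, and the sizes are therefore conditional.

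**A condensed article may leave arm to a fuller plan.** A fuller plan could indeed add it. But the article does more than stay silent: it names the predictor classes, and allocation belongs to neither. Service postcode, listed among educator demographics, might partly stand in for arm if entered as categories. Nothing says it will be, and it is not listed for parents.

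**Conclusion.** The point holds for the supplementary completer analysis only. Followed as written, the attrition model yields weights that cannot remove between-arm bias when attrition, or its dependence on baseline, differs by arm, although the article gives them the task of adjusting for any attrition bias. That conclusion is algebraic. The size is not: about 0.04 to 0.09 SD in the change contrast, or 7% to 17% of d = 0.5, rests on the assumed retention patterns and a pre-post correlation of 0.6.

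The documents do not show that attrition differs by arm, and if it does not, this bias is zero. By Time 3 the controls have also had the programme (that assessment comes "immediately after the control group has completed the intervention"), so the treated-versus-untreated comparison at risk is the one at Time 2. The change is worth making because, as planned, agreement between weighted and unweighted completers would say little about differential attrition.

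**What to change.** In Attrition analysis, state that the attrition model will be fitted separately by allocated arm or, equivalently in purpose, will include allocated arm and its interaction with the baseline value of the outcome being analysed. Weight completers by the inverse of the predicted probability of retention.

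Analyst blinding is no obstacle, since the masked group code described under Blinding can enter the model.

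The cost is one sentence, a few model terms and slightly more variable weights. With 118 educators, it is sensible to limit the interactions to the baseline outcome. Service-level covariates and stabilised weights are optional and not needed to correct this flaw.

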#### Educator questionnaire (collected at time 1, time 2, and time 3)

Using a variety of response types (e.g., Likert scales, dichotomous and open text responses) the questionnaire asks educators about their relationships with parents, how they work to engage with families, their confidence in communicating with families, and whether they refer families to support when needed. The questionnaire also asks educators about their skills and confidence in their interactions, specifically where a concern was discussed. Items in the questionnaire are from a variety of sources. Some items were devised by the project team, others have been adapted from the AusParenting in Schools Teacher Survey [20], and others are from our earlier ECEC Exploratory Study.

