#### Parent questionnaire (collected at time 1, time 2, and time 3)

At each time point we will ask parents about their relationship with educators, how welcome they feel at the service, how satisfied they are with the way educators communicate with them, and whether they have sought help from support services as a result of engaging with their child’s service. Items were devised by the project team and some were adapted from the Parenting Today in Victoria survey [21] conducted by the PRC, the Me as a Parent Scale [22], and the ECEC Exploratory Study.

If a parent has more than one child at the service, we ask them to select the child whose birthday is closest to the date on which they are filling out the questionnaire and respond to items with that particular child and that child’s educator as a reference point. In the case of twins or multiples, we ask parents to think of the eldest. Parents will be asked whether they have raised a concern with an educator and/or an educator has raised a concern with them, and how many times this occurred within the past 4 weeks. If this occurred, they will also be asked how satisfied they were with the interaction.

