### Trial outcomes

The primary outcomes of the trial are educator confidence and skills in working with parents, and parent satisfaction with interactions with their child’s educator. Secondary outcomes include parent inclusiveness at centre, supportiveness of centre, parenting involvement with their child’s centre and learning, staff satisfaction with using *Partnering with Parents*, parent satisfaction with discussing concerns with educators, and parent psychological distress (parenting competence and confidence, parenting stress). We expect there will be greater change from Time 1 to Time 2 for the intervention group than for the control group and we expect that the change will be maintained or further improved at three-month follow-up (Time 3).

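### Weights for Time 3 dropout are built from baseline variables alone, so the supplementary completer analysis leaves bias in within-arm change to Time 3, and can enlarge it, where dropout depends on Time 2 scores

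*Protocol article*

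**What the plan says.** The Attrition analysis section of the protocol article names one predictor set for both follow-up waves: "We will use binary logistic regression to model attrition at Times 2 and 3 in terms of baseline measures and demographic characteristics". It continues: "Predicted attrition probabilities for both these time points will be computed for use in completer analyses". In the section on analysis of primary and secondary outcome measures, these probabilities enter the closing analysis, a repeated measures MANOVA in completers, "using inverse probability weights to adjust for any attrition bias".

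The main analysis is a different one: "An intention-to-treat multi-level analysis will be conducted for each of the outcome measures", with the assessment periods as level 1. The weights are not mentioned there.

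Both the educator and the parent questionnaires are collected at all three times. Under Trial outcomes, the authors expect the Time 1 to Time 2 gain to be kept or to grow by Time 3. The Time 3 assessment takes place "immediately after the control group has completed the intervention".

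**The concern.** Weights built on baseline variables are valid for Time 3 only if dropout at Time 3 is unrelated to the Time 2 response once baseline is known. A parent who was dissatisfied at Time 2, or an educator whose confidence had fallen, may be less likely to answer again. Their Time 2 scores are in the data, but the stated rule does not use them. The completer analysis therefore rests on a stricter assumption than the multi-level model beside it, which does use observed Time 2 data.

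The part of the plan at stake is the follow-up hypothesis. By Time 3 the control services have also had the programme, so whether gains last is largely a question within the intervention arm. A within-arm bias does not cancel there. Selective dropout could look like loss or gain when nothing has changed. If the two analyses then disagreed, it would be unclear whether the model or the weights were at fault.

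**Working it through.** **What the documents give.** The article has no figure for the weights, for expected dropout or for correlations between waves. Its only attrition figures are the limits in the Power analysis section: 50% at ICC 3% and 33% at ICC 6%. These reproduce approximately. With 302 parents in 19 services and a required effective size of 102:

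- ICC 3%: 302 / [1 + (302/19 − 1) × 0.03] = 208.7, and 1 − 102/208.7 = 51%.
- ICC 6%: 302 / [1 + (302/19 − 1) × 0.06] = 159.5, and 1 − 102/159.5 = 36%.

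Losses of 36% and 50% are therefore about what the plan says it can tolerate. They are not forecasts.

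**Assumptions.** Scores have SD 1 and no true change. Correlations are r12 = r23 = 0.6 and r13 = 0.5. The log-odds of responding at Time 2 rise by 0.3 per SD of the Time 1 score. The log-odds of responding at Time 3 rise by 0.7 per SD of the Time 2 score. Loss is 25% then 33% (0.75 × 0.67 = 0.50 retained), or 20% then 20% (0.80 × 0.80 = 0.64 retained).

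**Why the weights fall short.** To first order, Time 3 dropout driven by the Time 2 score gives bias proportional to:

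- Time 1 to Time 3 change, unweighted: r23 − r12 = 0.6 − 0.6 = 0.
- Time 1 to Time 3 change, baseline weights: r23 − r12 × r13 = 0.6 − 0.30 = +0.30.
- Time 2 to Time 3 change, unweighted: r23 − 1 = −0.40.
- Time 2 to Time 3 change, baseline weights: (r23 − r12 × r13) − (1 − r12²) = 0.30 − 0.64 = −0.34.

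The weights restore the Time 1 mean fully but the Time 2 and Time 3 means only in part. For Time 2 to Time 3 change, 0.34/0.40 = 85% of the bias stays. For Time 1 to Time 3 change, a bias appears that dropout at this step had not caused.

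**Simulated bias in SD, 50% loss:**

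| Change | Unweighted | Baseline-only weights | Sequential weights with Time 2 |
|---|---|---|---|
| Time 2 to Time 3 | −0.09 | −0.08 | 0.00 |
| Time 1 to Time 3 | −0.04 | +0.06 | 0.00 |

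At 36% loss the baseline-only figures are −0.05 and +0.04. Over log-odds of 0.4 to 1.1 and both loss levels, the baseline-only bias in Time 2 to Time 3 change runs from −0.03 to −0.11 SD.

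**Other dropout patterns (same correlations, about 50% loss, Time 1 to Time 3 change).** With equal log-odds on the Time 1 and Time 2 scores (0.35 each), bias goes from −0.09 unweighted to +0.03 with baseline-only weights. With mainly baseline dependence (0.75 on Time 1, 0.25 on Time 2), it goes from −0.14 to +0.02. With baseline dependence only, the planned weights remove essentially all of it.

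**Between arms.** If dropout works alike in both arms, the between-arm bias is about zero. A further case assumed Time 2-dependent dropout in one arm only, with r12/r23/r13 = 0.5/0.7/0.5. The bias is +0.051 SD unweighted and +0.051 with baseline-only weights. It is +0.062 with Time 2 added but no arm terms, and +0.001 with arm and arm by Time 2 score included.

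**The case against.** Most of the case on the other side limits the point without removing it.

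- **Scope.** The weights enter only the closing completer analysis. The main multi-level model uses observed Time 2 data. In the within-arm simulations, a likelihood-type estimate using those data had bias of at most 0.003 SD. A reader might infer that the main estimate is biased, but the documents do not support that. Nor do they say that the MANOVA is there to check the main model. For change from Time 1 to Time 2, baseline variables and arm are the information available before dropout. This stands.
- **Size.** A reader might infer that the weights leave most of the attrition bias in place. That depends on how dropout works, on which the documents are silent. When dropout is mainly baseline-driven, the weights remove most of the bias in Time 1 to Time 3 change. The plan also uses several baseline measures and demographics, where the simulation uses one score. This stands.
- **Wording.** The phrase about adjusting for attrition bias can mean whatever bias there is. It need not be read as a promise of complete removal. This stands.
- **Precision.** With 59 educators per arm (118/2), weights fitted within arm and four extra uninformative covariates per wave, sequential weights had the higher root mean square error: 0.204 against 0.193 for Time 2 to Time 3 change, and 0.222 against 0.203 for Time 1 to Time 3. With 151 parents per arm (302/2) they did better. This stands and shapes the fix.
- **Detail left to an analysis plan.** This does not answer the point. The article does not leave the predictors open; it names them for both waves, and Time 2 scores are not among them.

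**Conclusion.** The point holds in a limited form. The stated rule omits recorded information that bears on Time 3 dropout. Where dropout depends on Time 2 scores, the weighted completer analysis keeps a within-arm bias in change to Time 3. For Time 1 to Time 3 change, that bias can exceed the unweighted one and have the opposite sign.

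Under the assumed correlations of 0.5 to 0.6 and log-odds of 0.7 per SD, the bias is about 0.04 to 0.08 SD at 36% to 50% loss. The upper end is 0.08/0.5 = 16% of the effect size used in the power section. The correlations and dropout slopes are assumptions, since the documents give none. The bias shrinks if baseline drives dropout, and it cancels between arms if dropout works alike in both. The main intention-to-treat analysis is not exposed if correctly specified and if dropout depends only on observed data.

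The change is worth making because the data will already be held. The Trial status section says follow-up had not yet been collected, so the rule could be fixed in advance.

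**What to change.** Build the weights in sequence.

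1. Model response at Time 2 from baseline variables and allocated arm.
2. Among Time 2 responders, model response at Time 3 from baseline variables, arm and a small pre-specified set of Time 2 outcome scores. Add arm by Time 2 score where numbers allow.
3. Weight each Time 3 completer by 1 / (p2 × p3), where p2 and p3 are the two predicted response probabilities, each equal to 1 minus the predicted attrition at that step.

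It would also help to say that the weights address attrition explained by the recorded variables, so that nobody reads more into the phrase.

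The cost is a change of analysis wording and more variable weights. For the 118 educators this can outweigh the gain if many predictors are used. Keep the predictor set short, and stabilise or truncate the weights by a rule fixed beforehand.
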